# 2. OBJECTIVES

Is the application of CryoSeal (CS) by primary total knee replacement surgery beneficial for the patient with respect to a faster track and improved early (2 and 6 weeks) postoperative rehabilitation as determined by improved knee extension. The beneficial effect may be due to quicker rehabilitation (focus on knee function), by pain reduction, better mobilisation and improved quality of life (especially short term).

.

# 3. STUDY DESIGN

The study is a randomised, multi centre trial in orthopaedic surgery in patients who receive a primary total knee replacement. Patients will be randomised in two groups. The intervention group will be treated with CryoSeal per operative and the control group will receive standard care (no additional treatment during surgery). Patients will be stratified prior to randomisation in six strata occording to the the clinical site where the use of postoperative wound drain is the standard procedure. No consensus between the sites exists on the usage of the latter.

Patients and observers will be blinded for treatment until 3 months postoperative.

See Flow chart next page

**Baseline**

Medical History- KSS

Knee function (F/E)- KOOS

Pain score- EQ5D

Handstrength- SF-12

Barthel Index score- IPQ-K

Oxford Knee Score

**Stratification and randomisation**

Patient meeting in- and exclusion criteria and willing to participate in the clinical trial

**CryoSeal**

**Usual care**

**Surgery**

**With or without**

**application of CryoSeal**

**Hospitalisation**

- Clinical data
- Complications
- Pain score
- Knee function F/E
- Barthel score (day 3)

**Outpatient department (2 weeks, 6 weeks and 1 year)**

- Complications (all timepoints)
- Pain score (all timepoints)
- Knee function F/E (all timepoints)
- KSS (6 wks, 1 year)
- Oxford Knee Score (OKS) (2, 6 wks, 1 year)
- Barthel index (2, 6 wks and 1 year)
- KOOS (6 wks and 1 year)
- SF-12 (6 wks and 1 year)
- IPQ-K (6 wks and 1 year)
- EQ5D (2, 6 wks and 1 year)

# 4. STUDY POPULATION

## 4.1 Population (base)

Patients older than 18 years of age, undergoing primary total knee replacement surgery are included. Since total knee replacement surgery is a well defined standardised surgical procedure and CS application can be standardised on the amount and the well defined layers of femoral and tibial and patellar ‘if applicable’.

## 4.2 Inclusion criteria

- Patients who will undergo primary total knee replacement surgery for osteoarthritis or rheumatic arthritis
- Age, minimum of 18 years
- (Admission of the patient after informed consent)
- ASA classification I-III
- Capable of reading and answering the Dutch language

## Exclusion criteria

- Liver failure
- Congenital or acquired coagulation disorders
- Patients with known haemophilia or von Willibrand disease
- Patients with INR >2 (standard practice for operation)

## 4.4 Sample size calculation

We performed a sample size calculation for our primary outcome which is pre- to postoperative difference in knee extension angle at two weeks after surgery. We expect to find a difference between study arms of 10 degrees, which we also feel is clinically relevant. We have little prior data to base our calculations on, but we expect a standard deviation of 35 degrees in our primary outcome. We conclude that we need 250 patients in each arm to be able to detect the stated difference at significance level 4.9% with 90% power.

We have made a slight adjustment to the usual significance level of 5% because we plan to perform an interim analysis when a total of 250 patients have been included. At this time we will decide if the trial should be terminated early for efficacy or futility. If the trial continues, we will use the available data to estimate the standard deviation of the primary outcome. Based on this estimate, we will re-compute the sample size that is needed to achieve 90% power to detect a 10 degree difference between the study arms at level 5%. We will adjust the sample size accordingly. However, we will not include less than 400 patients or more than 600 patients.

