## 6.5 Replacement of individual subjects after withdrawal

Withdrawal is not to be expected, as standard implants are being used and follow-up is not different from routine follow-up of knee prosthesis in general. If patients withdraw from the study they will not be replaced.

Patients that are already randomised but operation is rescheduled because of any reason, subjects will stay in the study without changing randomisation.

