# 8. STATISTICAL ANALYSIS

Data will be analysed by the intention-to-treat principle. Demographic characteristics, variables from laboratory analysis and quantitative variables obtained from the clinical evaluation (Pain score, opioids consumption) will be reported as means, medians or percentages together with their standard deviations, as appropriate.

We will perform the following analysis of the primary endpoint. In all patients we test for a difference in mean pre- and post-operative extension angles between those with and without Cryoseal. Adjusting for pre-operative extension angles by analysis of covariance, we perform a two-sided test at level 0.049. In a secondary analysis, Fisher’s exact test will be used to determine the effect of use of fibrin sealant on adverse events. We will investigate whether the Cryoseal effect is modified by the use of a drain by adding drain use and the interaction between drain use and Cryoseal to the above analysis of covariance model. Also, effects within various other patients groups will be studied (e.g. gender, age, adipositas and rheumatic disorders)

Interim analysis and stopping rule:

We plan to perform a single interim analysis when a total of 250 patients have been included. At this time we will decide if the trial should be terminated early for efficacy. In all patients we test for a difference in mean pre- and post-operative extension angles between those with and without Cryoseal. Adjusting for pre-operative extension angles, we perform a two-sided test at level 0.005. If we are able to reject the null hypothesis, we terminate the trial and conclude efficacy of the treatment.

If the stopping rule is not met and the trial continues, we must set the level of significance of the final analysis to 0.049 to account for the fact that we performed an interim analysis. This is referred to as the O'Brien-Fleming rule.

Also, if the trial continues, we will use the available data to estimate the standard deviation of the primary outcome. Based on this estimate, we will re-compute the sample size that is needed to achieve 90% power to detect a 10 degree difference between the study arms at level 5%. We will adjust the sample size accordingly. However, we will not include less than 400 patients or more than 600 patients.

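### The sample-size inputs give 259 per arm rather than 250, and the interim re-estimation uses a level and an SD that do not match the planned ANCOVA at 0.049

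*Combined protocol and SAP*

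**What the plan says.** Section 4.4 sizes the trial on "our primary outcome which is pre- to postoperative difference in knee extension angle at two weeks after surgery". Its assumptions are "We expect to find a difference between study arms of 10 degrees" and "we expect a standard deviation of 35 degrees in our primary outcome", and it concludes that "we need 250 patients in each arm to be able to detect the stated difference at significance level 4.9% with 90% power".

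Section 8 specifies the final test: "Adjusting for pre-operative extension angles by analysis of covariance, we perform a two-sided test at level 0.049".

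Both sections provide for a re-estimation at the interim, when 250 patients in total have been included. If the trial continues, "we will use the available data to estimate the standard deviation of the primary outcome", and the new N is to give "90% power to detect a 10 degree difference between the study arms at level 5" percent. The total is held between 400 and 600. Neither section mentions a residual or baseline-adjusted SD.

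There is no allowance for missing angles. Section 6.5 adds: "If patients withdraw from the study they will not be replaced".

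**The concern.** The figure of 250 does not follow from the inputs printed beside it.

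The re-estimation matters more. Section 4.4 concedes that there is little prior information on the SD, so the interim rule, not the 35-degree assumption, is likely to set the final N. That rule is not aligned with the analysis it serves:

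- **Level.** N is recomputed at 5%, while section 8 fixes the final level at 0.049.
- **SD.** Taken with the definition in section 4.4, the SD named is that of the change score. The error term of the planned ANCOVA is the residual SD after adjusting for the pre-operative angle, and this is no larger than the change-score SD.

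The two slips act in opposite directions. The level makes N slightly too small. The SD can make it substantially too large, so that more patients are recruited than 90% power requires.

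**Working it through.** **Inputs.** Difference 10, SD 35 for the change, level 4.9% and power 90% (section 4.4). The test is two-sided by ANCOVA on the pre-operative angle at 0.049, and the re-estimation is at 5% with limits of 400 to 600 (section 8). Arms are of equal size (section 6.2).

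**1. The plan's figure.** For two means, n per arm = 2 × (z for 1 − α/2 + z for power)² × (SD/difference)².

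2 × (1.969 + 1.282)² × (35/10)² = 258.8 with unrounded quantiles, so 259 per arm.

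Power at 250 per arm: 10 / (35 × √(2/250)) = 3.194, and Φ(3.194 − 1.969) = 89.0%.

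Other routes to 250 were tried:

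| Calculation | n per arm |
|---|---|
| Two-sided 4.9%, normal | 259 |
| Two-sided 5%, normal | 258 |
| Two-sided 4.9%, t-test | 260 |
| Two-sided 5%, t-test | 259 |
| Counting the interim look (0.005, then 0.049) | 258 |
| One-sided 4.9% | 212 |
| One-sided 5% | 210 |

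None gives 250. Counting the interim look, power at 250 per arm is 89.1%.

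**2. Level in the re-estimation.**

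| SD | n per arm at 5% | n per arm at 4.9% |
|---|---|---|
| 30 | 190 | 191 |
| 33 | 229 | 231 |
| 35 | 258 | 259 |
| 37 | 288 | 290 |

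The plan's rule is short by 1 to 2 per arm. Power at 0.049 is then about 89.9%.

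**3. SD in the re-estimation.** A change score fixes the baseline slope at 1, whereas ANCOVA fits the slope that minimises residual variance. The residual SD therefore cannot exceed the change SD, and the two are equal only at a slope of 1. The documents do not give the pre-post correlation r, so it is assumed here, with equal pre and post variances σ²:

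- change variance = 2σ²(1 − r)
- residual variance = σ²(1 − r²)
- ratio = (1 + r)/2

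The n per arm for ANCOVA at 0.049 is then 258.8 × (1 + r)/2, rounded up. At a change SD of 35 the plan's rule gives 2 × 258 = 516 in total.

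| Assumed r | Residual SD | n per arm | Total N | Excess of 516 over the larger of N and 400 | ANCOVA power at 250 per arm |
|---|---|---|---|---|---|
| 0.3 | 28.2 | 169 | 338 | 116 | 97.7% |
| 0.5 | 30.3 | 195 | 390 | 116 | 95.7% |
| 0.7 | 32.3 | 220 | 440 | 76 | 93.3% |
| 0.9 | 34.1 | 246 | 492 | 24 | 90.5% |

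**4. Where 250 per arm suffices under ANCOVA.** This needs (1 + r)/2 ≤ 250/258.8 = 0.966, so r up to about 0.93, or a residual SD of 34.4 or less.

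**5. The cap.** At 600 in total, 90% power at 0.049 holds up to a residual SD of 10 × √(300/2) / (1.969 + 1.282) = 37.7. The 400 floor costs no power; below a residual SD of about 30.8 it gives more than 90%.

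**The case against.** A reader might infer from 259 against 250 that the trial is underpowered, the more so because withdrawals are not replaced. For an unadjusted change-score comparison, power would be 87.4% with an assumed 5% missing and 85.6% with 10%. But that is not the planned test. Under the planned ANCOVA, 250 per arm gives 93% to 98% for r from 0.3 to 0.7. With 10% missing (225 per arm) it still gives 96.3%, 93.7% and 90.6% at r = 0.3, 0.5 and 0.7. The documents do not support a finding of inadequate power. They support only that the printed figure does not follow from the printed inputs.

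It can also be said that the gap is one percentage point around an admittedly uncertain SD, that the re-estimation will replace that SD, and that the 5% slip is trivial. All of this stands.

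On the SD, the plan does not say how it will be estimated, and an adjusted estimate may have been meant. That is possible, but section 4.4 defines the primary outcome as the change and nothing points to a residual SD. Using the change SD is also safe for power, since its cost is extra patients. The size of that cost rests on an r that the documents do not give. At r = 0.9 it is about 25 patients, and at a baseline slope of 1 it vanishes. A large excess is therefore a possibility over a plausible range, not an established result.

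**Conclusion.** The point holds as an arithmetic error and a specification mismatch, of low to moderate practical weight.

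- The stated inputs need 259 per arm, and 250 gives 89%. Both figures are for the unadjusted change score.
- The 5% level in the re-estimation contradicts the final level of 0.049 and costs 1 to 2 patients per arm.
- The SD named for the re-estimation does not match the ANCOVA. At a change SD of 35 and after the 400 floor, the excess is about 75 to 115 patients for r of 0.3 to 0.7, and about 25 at r = 0.9. This assumes equal pre and post variances and that the SD is read as section 4.4 defines it.

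The 5% level does not explain the figure of 250, so the initial error and the re-estimation inputs are separate matters.

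**What to change.** In section 4.4, state 89% power at 250 per arm, or 259 per arm for 90%, and say that the calculation is for the unadjusted change score.

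In sections 4.4 and 8, re-estimate N at 0.049 from the residual SD of the same ANCOVA as the final analysis, adjusting for the pre-operative angle. Keep the 400 and 600 limits, and report the attained power if the 600 cap binds (residual SD above about 37.7).

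The cost is some rewording, one changed level and one changed SD, with no extra visits or data. The downside is that the stated power reads slightly less favourably.

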# 5. TREATMENT OF SUBJECTS

## 5.1 Investigational product/treatment

ThermoGenesis (in the Netherlands represented by MDM) is a company that manufacturers a device for the production of fibrin sealant from single donor plasma, the CryoSeal Fibrin Sealant System (CS-1). Due to a low plasminogen concentration in the cryoprecipitate no fibrinolysis inhibitors are needed.

The following product developing activities are foreseen:

1. CS-maintenance longer than 2 years after production; 2. CS-Packing; 3. Cryo-poor plasma (re)use; 4. Development of custom-made (friendly use) disposables in collaboration with ThermoGenesis and MD-management.

Fibrin sealant will be produced and released from SBNO according to the operational production procedures. The production of fibrin sealant has been validated according the procedure VP-P.06.233. The quality criteria for fibrin sealant are: Cloth test: cloth formation < 10s; Qualitative FXIII test: no cloth resolving in 24h.

Preparation and application of the fibrin sealant

- The first procedures of fibrin sealant application was performed under supervision of experts from MDM. From these data it was decided to use two syringes of 5 ml each.
- Fibrin sealant will be used on the day of surgery in the operation room as follows:
- Thaw the fibrin sealant at 30-37°C, which takes about 10 minutes for the over wrapped fibrin sealant. Note: The thrombin and cryoprecipitate preparations from the cryoprecipitate system (CP-3) can be stored on ice for up to 4 hours, with 2 additional hours at 34-37°C or stored up to 6 hours at 34-37°C after which time they must be discarded.
- At the time of application as chosen by the surgeon, the fibrin sealant in the sterile field will be put as follows: Press on the locking bar inside the sterile over wrap to release the paired syringes from the plastic end connector (circulating nurse). Peel open the over wrap bag and present the paired syringes to another person (scrub nurse), who grasps only the end cap joining the two plungers and places the syringes into a tray in the sterile field. Repeat this for each set of paired syringes that is required for the patient.
- Assemble and load the FS Applicator with the fibrin sealant (scrub nurse).
- The circulating nurse peels the sterile over wrap of the Spray (ST-3) and drops it in the sterile field.
- FS Applicator tip is held facing upwards and the syringes lightly tapped to allow air bubbles to rise to the tip of the syringe (scrub nurse).
- The scrub nurse gently squeezes the plunger to expel any air bubbles into a sterile wipe, following this step a sterile luer lock stopcock, as available in the OR, will be placed on each of the Applicator tips transferred.
- Next the cryoprecipitate and thrombin preparations present inside the 3 cc paired syringes are prewarmed to 34-37°C during a 20 minute period. (To be used for pre-warming is the warning cabinet as present at the OR. The warming cabinet is to be set at a maximum temperature of 40°C. During pre-warning the CryoSeal pouches should NOT get in contact with any metal components inside the warming cabinet. Best is to place the CryoSeal (Cryolijm) pouches in a carton kidney-“bekkentje” available at anaesthesiology). After approximately 20 minutes the CryoSeal Fibrin Sealant, now pre-warmed to 34-37°C, is ready for use in the surgery field.
- The Fibrin Sealant will be applied to the surgical site. Two application techniques are possible. First, the kneeprothesis procedure is performed without the use a bloodbarrier until cementation of the prosthesis. In this technique the FS can be applied immediate after cementing the knee. A second technique is that the bloodless field is opened surgically temporarily to stop more extensive haemorrhaging via diathermy. Subsequently, pressure is re-applied followed by the application of the fibrin glue via the spray applicator on the surfaces of the dry wound bed. Furthermore the following steps are used: **A)** by holding the FS Applicator such that the tip is pointing toward the area targeted for haemostasis, **B)** positioning the tip approximately 7.5 – 8 cm from the surface of the target tissue, and **C)** pressing the plungers of the paired syringes while moving the hand in an “air brushing” back and forth type motion to create a homogeneous layer of fibrin sealant covering 15-17 square cm of target tissue per 1 mL of Fibrin Sealant. After waiting approximately 30 seconds, a second tip (ST-3) can be used to lay down a second layer of fibrin sealant on top of the first, following which a check for haemostasis should take. Vascular control is to be maintained throughout the application of the product.

## 5.2 Summary of known and potential risks and benefits

Given the origin of the CryoSeal™ product, i.e. donor plasma and in the absence of added bovine or chemical fibrinolysis inhibitors, no toxicity was / is to be expected by applying CryoSeal™ produced by the CS-1 (machine) / CP-3 (disposable) system, which was confirmed by pre and clinical research.

# 6. METHODS

## Study parameters and endpoints

Hypothesis

The hypothesis is that the application of CryoSeal (CS) during total knee replacement surgery is beneficial for the patient with respect to a faster track and improved postoperative rehabilitation. The beneficial effect may be due to quicker rehabilitation, by pain reduction, better mobilisation and quality of life (especially short time).

Primary endpoints

- postoperative knee function in extension difference as compared with preoperative extension function with goniometric at 2 and 6 weeks (in relation to secondary endpoints)

Secondary endpoints

- Grade flexion and extension difference after surgery
- Drain use or not
- Postoperative Hb/Ht
- Number of transfusions after surgery (according to appendix 1)
- Pain score
- Complications
- Total hospital stay and duration of rehabilitation
- Illness perception IPQ-K score
- Function improvement score (KSS, Barthel Index score, KOOS etc. see flowchart)
- Hand grip strength (measured with (Jamar) hand dynamometer)
- Activity Monitor

Study parameters

- Demographic data; gender, birth date (age), weight, length (BMI)
- Medical History; underlying diseases and home medication (including use of antibiotics prophylaxis and NSAIDs)
- Laboratory analysis; haemoglobin, haematocrit and blood view, CRP and erythrocyte sedimentation rate
- Operation details; anaesthesia, start- and end time of surgery, surgeon, type and time point placing and opening of drain, use of heparin, information about application of CryoSeal (if applicable), knee function after implantation of the implants
- Clinical data; number of transfusions (red cells, platelets and plasma), complications, removing drain, amount collected in drain, medication (including use of antibiotics and NSAIDs), discharge date
- Pain (score) at 24h post operative, and at 8:00 h each day until discharge from hospital.
- Rehabilitation; knee function during the first postoperative days, Barthel Index score and standard knee function scores (see Table 1).
- Handstrength measurement: is used as a proxy of muscle strength and measured by three maximal squeezes with both, the right and left hand applied at a hand held dynamometer (Jamar hand dynamometer, Sammons Preston Inc, Bolingbrook, IL)). Subjects are asked to stand up and hold the dynamometer in the hand with the arm parallel to the body without squeezing the arm against the body. The width of the handle is adjusted to the size of the hand to make sure that the middle phalanx rested on the inner handle. The participant is allowed to perform one test trial. After this, three trials are performed and the best score is taken for analysis. Handgrip strength is expressed in kilograms.

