# SUMMARY

**Rationale:** Fibrin Sealant is known to have some potential benefits for intraoperative use, especially in the acceleration of the coagulation cascade. Most studies with fibrin glue are focussing on the reduction of allogeneic blood transfusion and the possibilities to reduce costs. Firstly, fibrin sealant was made from patients’ blood plasma but the logistic problems made introduction in general hard. Now Sanquin has produced a CryoSeal (fibrin sealant) made of single-donor plasma which can be used during surgery. This application is already used in cardiothoracic surgery.

**Objective:** Is the application of CryoSeal (CS) in primary total knee replacement surgery beneficial for the patient with respect to a faster track and improved postoperative rehabilitation. The beneficial effect may be due to quicker functional knee rehabilitation, by pain reduction, better mobilisation and improved quality of life during the early postoperative period.

**Study design:** Multicenter, randomised controlled trial stratified by clinic.

**Study population:** Patients aged above 18 years scheduled for primary total knee replacement (TKA) because of osteoarthritis or rheumatic arthritis, meeting all the inclusion criteria and none of the exclusion criteria, are eligible for inclusion in the study.

**Intervention:** The intervention is the application of CryoSeal during surgery according to the standardised manner. The control group will receive standard care.

**Main study parameters/endpoints:** Primary endpoint: Difference in extension knee function 2 and 6 weeks after surgery. Secondary endpoints: postoperative complications, Pain score, knee function Flexion/Extension, Barthel score (day 3); Outpatient department scores (2 weeks, 6 weeks and 3 months, 1 year): Complications, Pain knee function, KSS, KOOS, SF-12, IPQ-K and EQ5D. A pre- and postoperative hand strength measurement will be performed since this might be a predictor of outcome after TKA. (Taekema 2010). Where possible, an actual physical activity measurement will take place to objectively analyse pre- and post operative acitivity level. (Groot, de 2008)

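### The documents disagree on whether the primary endpoint is knee extension at 2 weeks or at 2 and 6 weeks, and the stated error rate and approximate power hold together only for 2 weeks alone

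*Combined protocol and SAP*

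**What the plan says.** Three places put the primary endpoint at two times:

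- Summary: "Primary endpoint: Difference in extension knee function 2 and 6 weeks after surgery".
- Section 2, Objectives: "improved early (2 and 6 weeks) postoperative rehabilitation as determined by improved knee extension".
- Section 6, Study parameters and endpoints, under a plural heading for primary endpoints: "postoperative knee function in extension difference as compared with preoperative extension function with goniometric at 2 and 6 weeks".

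Section 4.4, the only basis for the number of patients, has one time: "our primary outcome which is pre- to postoperative difference in knee extension angle at two weeks after surgery".

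Section 8 gives the test but no time: "In all patients we test for a difference in mean pre- and post-operative extension angles between those with and without Cryoseal". At the final analysis, "Adjusting for pre-operative extension angles by analysis of covariance, we perform a two-sided test at level 0.049"; at the interim, "Adjusting for pre-operative extension angles, we perform a two-sided test at level 0.005". It has no either/both rule and no model that combines the two visits. It justifies the 0.049 level by the interim look alone.

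The addendum of 15 May 2013 refers the primary analysis back to the protocol and uses the plural for the primary end points. Its statement that no multiplicity correction will be made concerns the subgroup analyses, not the two time points.

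**The concern.** This is conflicting current text about the confirmatory hypothesis, not a missing detail. Three decisions depend on it:

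- **The final claim.** With two candidate time points and no rule for the pair, an analyst could settle the reading after seeing which time point is significant, and nothing written would prevent it.
- **The early stop.** The interim can end the trial for efficacy, and the time point that triggers this is not named.
- **The sample size.** Re-estimation uses the SD of the primary outcome to set N between 400 and 600. With two primary time points, it is unclear which SD that is.

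The levels 0.005 and 0.049 allow for two looks at one endpoint. They leave nothing for a second time point.

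**Working it through.** **Inputs from the documents.** Difference 10 degrees, SD 35 degrees, 250 per arm, two-sided level 0.049, target power 90% (section 4.4); interim level 0.005 at 250 patients in total (section 8). With 500 patients planned, the information fraction at the interim is 250/500 = 0.5.

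**Assumed, because the documents do not give it.** The correlation ρ between the 2-week and 6-week test statistics, taken from 0 to 0.8. For the both-required reading, also the same effect and SD at 6 weeks as at 2 weeks.

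**Critical values.** Two-sided 0.049 gives c = 1.969; two-sided 0.005 gives 2.807.

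**Step 1: the plan's own figure.** n per arm = 2 × 35² × (1.969 + 1.282)² / 10² ≈ 259, against the stated 250. At 250 per arm the standard error is 35 × √(2/250) = 3.130, the standardised effect is 10/3.130 = 3.194, and power is Φ(3.194 − 1.969) = 0.890. The stated N is slightly low, at a cost of about one point of power. This does not affect the present point.

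**Step 2: 2 weeks as sole primary.** The chance under the null of crossing 2.807 at the interim or 1.969 at the final look, with correlation √0.5 between looks, is 0.0509. It is 0.0501 if the final N is 400 and 0.0514 if it is 600. Power is about 0.89 from Step 1.

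**Step 3: either time point counts.** At the final look the rate is 1 − P(|Z1| < 1.969, |Z2| < 1.969). For ρ = 0 this is 1 − 0.951² = 0.0956. Adding the interim at 0.005 on both time points, for ρ = 0, gives 1 − (1 − 0.0509)² = 0.0992; the other values with the interim were simulated at information fraction 0.5.

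**Step 4: both time points required.** The false-positive rate is at most that of a single test: 0.049 at the final look, about 0.051 with the interim. Power at the final look is P(Z1 > 1.969, Z2 > 1.969) with both means at 3.194. For ρ = 0 this is 0.890² = 0.792.

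| Assumed ρ | Either: final look | Either: with interim | Both: power |
|---|---|---|---|
| 0 | 9.6% | 9.9% | 0.79 |
| 0.3 | 9.3% | 9.7% | 0.80 |
| 0.5 | 8.9% | 9.2% | 0.82 |
| 0.8 | 7.7% | 8.0% | 0.84 |

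**The case against.** A reader might infer that the plan has a false-positive rate of 8% to 9%. The documents do not support that as a statement of fact. Section 8 describes one two-sided test at each look, and section 4.4 has one primary outcome at 2 weeks. Joining those two sections gives a single test with overall alpha of about 5.1%. No section says that both time points are each tested at 0.049, or that either one suffices, and no correlation is given. A final-look rate between 8% and 9% needs ρ between about 0.46 and 0.74, which is an assumption. A single test combining the two visits would also add no inflation, though none is described. This objection stands: the text permits inflation but does not establish it. Nor do the documents suggest that anyone means to choose the time point afterwards.

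The power contrast also needs care. A single endpoint already has 0.89 rather than 0.90, so the both-required reading costs about 5 to 10 points relative to 0.89, and only if the effect and SD at 6 weeks equal those at 2 weeks.

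Finally, making 2 weeks the sole primary is not the only sound remedy, since the objective names both times. That is fair, but each alternative has to be stated with its alpha and its sample size.

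None of this removes the contradiction. The reading that preserves the planned properties is at odds with the Summary, section 2 and section 6.

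**Conclusion.** The point holds as a contradiction over the primary endpoint, and it should be resolved before de-blinding. Confidence is high on the contradiction, because it rests on the text alone. The sizes are conditional. The either-one figures depend on a success rule that the plan neither states nor excludes, and on the assumed correlation. The both-required power depends on that correlation and on carrying the 10 degrees and SD of 35 over to 6 weeks. Of these three readings, only 2 weeks alone gives both an overall alpha near 5% and power near 90%.

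**What to change.** In the Summary, sections 2, 4.4, 6 and 8, and the addendum, name the 2-week change in knee extension as the single primary endpoint. State that it governs the interim test, the final test and the SD used in the sample-size re-estimation. Make 6 weeks the first key secondary endpoint, tested at the same level only if the 2-week test is significant. This fixed sequence needs no split of alpha, no more patients and no new data.

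The cost is that a 6-week effect alone cannot be claimed as the primary result. The change must also be notified to the ethics committee (METC) as an amendment (section 10.2) and be in place before de-blinding.

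If the sponsor prefers to keep two primary time points, the rule and its consequences must be written down. An either-one rule with the final level halved (0.0245 each) needs 306 per arm for 90% power at a given time point. That is 612 in total, above the plan's cap of 600; with 250 per arm, power is 0.83. A both-required rule can keep 0.049 for each test but must accept the lower power shown above or a larger N.
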